##### Blood Collection

Fasting blood draws are collected. From a chemistry 15 panel, blood glucose, albumin, triglycerides, and cholesterol (total, low-density lipoprotein, and high-density lipoprotein) levels are measured. In addition, DHEA-S, CRP, thyroid-stimulating hormone, free tri-iodothyronine, free thyroxine, and insulin levels are measured.

##### Urinary Cortisol

Urinary cortisol level is obtained from 24-hour urine collections. Participants are provided instructions, a urine hat, and a urine jug. Participants perform the first 24-hour urine collection within 3 days (ideally within 24-48 h) before clinic visit 1. An immunoassay with chemiluminescent detection is used to determine cortisol concentration from urine.

##### Allostatic Load

An *allostatic load total score* is calculated from selected clinic assessments described previously [55].

Textbox 2 presents each psychological and physiological parameter assessed in the RESPONSES study, as well as the relevant questionnaire or metabolic or endocrine assessment used to measure each parameter.

#### Questionnaires

##### Health Literacy

The Rapid Estimate of Adult Literacy in Medicine–Short Form (REALM-SF) is used to measure health literacy in participants. This assessment is a standardized series of 7 words. The score (0-7) provides an assessment of how well a participant will be able to understand the additional questionnaires. Participants scoring 0 to 3 on the REALM-SF are aided by study staff in completing the other questionnaires. Patients scoring 4 to 7 on the REALM-SF complete the other questionnaires on their own but are offered assistance as needed.

##### Food Security Status

This is measured using a modified version of the 6-item Food Security Scale [56,57]. This scale is a well-validated measure of food security developed by researchers at the National Center for Health Statistics. Two or more affirmative answers indicate food insecurity.

##### Food Assistance

Participants will be asked about their use of federal food assistance (eg, SNAP [food stamps] and Special Supplemental Nutrition Program for Women, Infants, and Children) and other forms of nonfederal food assistance (eg, visits to food pantries and soup kitchens).

##### Sociodemographics

Participants complete a questionnaire that assesses age (date of birth), race, ethnicity, sex, marital status, the highest level of education completed, annual household income, the number of people in the household, occupation, employment status, home street address (including city and zip code), sources of financial support, dependent status, insurance and health care coverage, and smoking status.

##### Dietary Quality

A screener that assesses dietary fat, fruit, vegetable, and alcohol intake is completed by participants. The screener contains scales from several sources. The National Cancer Institute fat screener estimates the percentage of energy from fat by asking participants to report the frequency of consuming specific foods over the past 12 months [58,59]. A standard 7-item fruit and vegetable screener developed by the National Cancer Institute and the National 5 a Day Program asks how often fruit and vegetables were consumed in the past month [60,61]. Three questions related to the frequency of alcohol (beer, wine, and hard liquor) intake were adapted from the Brief Questionnaire to Assess Habitual Beverage Intake [62].

#### Psychological Questionnaires

Participants also complete multiple self-report questionnaires to measure psychological constructs related to stress; executive function, decision-making, and motivation; and affect and nonhomeostatic eating, as well as overall well-being, physical activity, and sleep. All questionnaires are reliable and valid as described in the following subsections.

##### Perceived Stress Scale

The Perceived Stress Scale-10 (PSS-10) is the most widely used psychological instrument to measure the perception of stress [63]. This questionnaire includes 10 items that measure the degree to which situations in one’s life are appraised as stressful. The PSS-4 is a shortened version of the PSS-10 designed for telephone interviews. Items are designed to tap how unpredictable, uncontrollable, and overloaded respondents find their lives. Higher scores on the PSS-10 and PSS-4 indicate greater stress.

##### Subjective Social Status

This construct indicates one’s self-perceived social position in American society and will be measured using the MacArthur Scale of Subjective Social Status [64]. This scale presents a *ladder* and asks participants to select a rung on which they feel they stand compared with other people in the United States. Scores range from 1 to 10, with higher scores representing higher subjective social status.

##### Kirby 27-Item Monetary Choice Questionnaire

Delay discounting is a bias toward smaller immediate rewards versus larger delayed rewards [65] and will be assessed via the Kirby 27-item Monetary Choice Questionnaire [66]. This questionnaire presents participants with a set of choices between smaller immediate monetary rewards and larger delayed monetary rewards. Participants who discount the value of the delayed rewards more steeply are considered to be more impulsive [66].

##### 8-Item Short Grit Scale

Grit is a measure of trait-level perseverance and passion for long-term goals and will be assessed using the 8-item Short Grit Scale [67]. Scores range from 1 (not at all gritty) to 5 (extremely gritty).

##### Zimbardo Time Perspective Inventory–Future Scale

Future time perspective is a comprehensive assessment of one’s orientation toward the future [47,68]. The *future* scale of the Zimbardo Time Perspective Inventory measures psychological orientation toward the future [69]. This scale comprises 13 statements with Likert-type responses. Higher scores indicate greater future time perspective.

##### Consideration of Future Consequences Scale

This scale is a valid and reliable 14-item measure of the extent to which a participant considers future outcomes in relation to current behaviors. The measure assesses two subscales—(1) consideration of immediate consequences and (2) consideration of future consequences—to assess the extent to which a participant feels that they may be influenced by an abstract consequence. The participant indicates how much they agree with the statement on a scale from 1 (not at all like you) to 7 (very much like you) [70-72]. Higher scores indicate greater consideration of future consequences.

##### Financial Planning

Participants will be asked a single question to assess the time period considered for financial planning: “In planning your, or your family’s, saving and spending, which of the following time periods is more important to you and your partner, if you have one?” with the following response options: no planning, day to day, the next few weeks, the next few months, the next year, the next few years, the next 5 to 10 years, longer than 10 years [73,74]. Higher values indicate greater future time perspective.

##### Longevity

Participants’ subjective appraisal of longevity will also be assessed via a single question: “What do you think are the chances you will live to age 75 or more (where 0 means there is not a chance you will live to 75 or more, and 100 means you will definitely live to 75 or more)?” [73,74]. Higher values indicate greater future time perspective.

##### Retrospective Visual Analog Scale

This scale contains 9 items to measure the average ratings of appetitive sensations that participants experienced over the past week. This method of collecting visual analog scale data has been found to be consistent with daily assessments of satiety [52], and support has been found for the reliability and validity of the visual analog scale for measuring subjective states related to energy intake [53].

##### Positive and Negative Affect Schedule

This is a self-report measure that is made up of 2 mood scales, 1 measuring positive affect and 1 measuring negative affect [75]. It has 10 items measuring positive affect and 10 items measuring negative affect on a 5-point Likert scale ranging from 1 (very slightly or not at all) to 5 (extremely). Scores can range from 10 to 50 on each scale, with higher scores representing higher levels of positive affect and lower scores representing lower levels of negative affect.

##### Psychological Distress

The Kessler Psychological Distress Scale (short version) is a 6-item self-report measure of psychological distress [76]. Respondents indicate how often they have had 6 different feelings or experiences during the past 30 days using a 5-point Likert scale: 4 (all of the time), 3 (most of the time), 2 (some of the time), 1 (a little of the time), and 0 (none of the time). The feelings and experiences are the following: *nervous*, *hopeless*, *restless or fidgety*, *so depressed that nothing could cheer you up*, *that everything was an effort*, and *worthless*. The score ranges from 0 to 24, with higher scores indicating greater psychological distress.

##### Food Craving Inventory

This is a 33-item measure of food craving [77,78] and assesses the frequency with which an individual experiences a craving for a particular food. The measure consists of 5 empirically derived factors: high fats, sweets, carbohydrates and starches, fruits and vegetables, and fast-food fats.

##### Food Craving Questionnaire-State

This questionnaire was developed to measure state (at the moment) craving for food using 15 items [79]. The reliability and validity of the state version of the Food Craving Questionnaire have been established.

##### Eating Disorder Diagnostic Scale

This brief scale contains 18 self-report items to assess eating disorder pathology and has been shown to be reliable and valid [80]. This measure can diagnose anorexia nervosa, bulimia nervosa, and binge eating disorder.

##### Yale Food Addiction Scale

This is a 27-item self-report questionnaire [81] used to identify individuals showing tendencies for addictive-like behaviors toward certain types of foods, such as those high in fat or sugar. The measure also allows participants to subjectively identify specific problem foods.

##### Eating Inventory

The Three-Factor Eating Inventory is designed to measure different dimensions of eating behavior. Three factor-analyzed subscales (cognitive restraint, disinhibition, and hunger) are derived from the questionnaire [82]. The 51-item questionnaire is divided into 2 parts: part I is composed of 36 true-false items, and part II is composed of 15 rating scale items.

##### Power of Food Survey

The PFS measures loss-of-control, or nonhomeostatic, eating. The PFS comprises 15 items that use a 5-point Likert scale to assess the intensity of desire to consume delicious food when not hungry [51]. Higher scores indicate greater hedonic hunger.

##### Patient-Reported Outcomes Measurement Information System-43

The Patient-Reported Outcomes Measurement Information System (PROMIS) is a system of highly reliable and precise measures of patient-reported health status for physical, mental, and social well-being [83,84]. The PROMIS-43 is a 43-item health-related quality-of-life questionnaire that includes questions covering the health-related domains of physical function, anxiety, depression, fatigue, sleep disturbance, ability to participate in social roles and activities, pain interference, and pain intensity.

##### International Physical Activity Questionnaire–Long Form

This is a 7-day recall of the intensity of physical activity and has acceptable reliability [85]. The results are reported as a continuous measure in median metabolic equivalent of task minutes per week.

##### Pittsburgh Sleep Quality Index

This is a self-rated questionnaire to assess sleep quality and disturbance over a 1-month time interval [86]. A total of 19 individual items generate 7 *component* scores: subjective sleep quality, sleep latency, sleep duration, habitual sleep efficiency, sleep disturbances, the use of sleeping medication, and daytime dysfunction. The sum of the scores for these 7 components yields 1 global score. Acceptable measures of internal homogeneity, consistency (test-retest reliability), and validity have been obtained [86].

##### Resource Packet

Given the focus on women who experience food insecurity, a resource packet was developed for the RESPONSES study that identifies community resources and services available to participants who may face resource deficits that compromise their overall health. Importantly, participants may identify multiple resource deficits beyond food insecurity during their participation in the study. The resource packet includes relevant community resources and services that address a range of health-related issues and concerns, including food insecurity, medical and dental care, mental health, substance abuse, and domestic violence. The resource packet is given to all participants regardless of study completion or food security status.

### Management of Study Data

Portions of RESPONSES study data are collected and managed using Research Electronic Data Capture (REDCap; Vanderbilt University) hosted at Pennington Biomedical Research Center. REDCap is a secure Health Insurance Portability and Accountability Act–compliant web-based application designed to support data capture for research studies, providing (1) an intuitive interface for validated data entry, (2) audit trails for tracking data manipulation and export procedures, (3) automated export procedures for seamless data downloads to common statistical packages, and (4) procedures for importing data from external sources [87].

### Sample Size and Statistical Power

Change in body weight was used to compute a minimum sample size for at least 80% power to examine response to episodic food insecurity longitudinally in African American women with obesity. Specifically, the power analysis is based on a study by Wilde and Peterman [23], which used nationally representative data to examine change in body weight over a 1-year period by food security status in women and men. We chose these data on body weight because we expect this measure to be responsive to episodic food insecurity. Wilde and Peterman [23] found that food-secure women had a 10.4% chance of gaining between 2.27 kg and 4.54 kg and a 20.7% chance of gaining >4.54 kg during a 1-year period. Food-insecure women had a 13% chance and a 31.7% chance of gaining between 2.27 kg and 4.54 kg and >4.54 kg, respectively. Using these estimates, an expected change over 22 weeks in the food-secure group is 0.54 kg, and an expected change in the food-insecure group is 0.80 kg. An SD of 22-week change in body weight, 0.24 kg [88], was increased to 0.30 kg to account for higher variability and ensure that the proposed study is well powered. Thus, with 60 participants, the study is well powered (>80%) to detect differences in body weight changes for aim 1. Furthermore, this study is also powered to detect a correlation as small as 0.40 for aim 2.

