## Methods

### Overview of Study Design

This study is a 22-week longitudinal observation cohort study conducted at Pennington Biomedical Research Center in Baton Rouge, Louisiana. A total of 60 African American women with obesity—30 (50%) who report being food insecure and 30 (50%) who report being food secure at baseline—have been enrolled in the study. Daily body weights are remotely obtained from participants. Wearable devices are also given to participants to wear throughout the duration of the study to collect additional data. Weekly food security status and stress assessments are remotely conducted to ascertain episodes of food insecurity and self-reported stress. Psychological and physiological parameters are measured at the beginning (week 0 at clinic visit 1) and conclusion (week 22 at clinic visit 3) of the study. There is also a midpoint remote assessment of selected psychological parameters (week 11 at remote visit 2). Figure 1 presents the RESPONSES study design and timeline.

The study was registered at ClinicalTrials.gov (NCT05076487) on September 30, 2021.

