### Aims

The RESPONSES study will address the following aims.

Aim 1: the study will longitudinally assess body weight in addition to psychological and physiological parameters in food-insecure and food-secure African American women with obesity. Body weight is collected to assess the change from week 0 to week 22. Psychological parameters (stress; executive function, decision-making, and motivation; and affect and nonhomeostatic eating) are measured via validated questionnaires. Physiological parameters are measured via 24-hour urine (cortisol) and blood (dehydroepiandrosterone-sulfate [DHEA-S], C-reactive protein [CRP], thyroid hormones, blood glucose, glycated hemoglobin, and insulin) samples as well as an allostatic load total score. These parameters are measured at week 0 and week 22 to examine changes in psychological and physiological mechanisms. We hypothesize that food-insecure African American women with obesity will demonstrate increased body weight and changes in psychological and physiological parameters consistent with elevated stress over 22 weeks compared with food-secure African American women with obesity.Aim 2: the study will examine associations between changes in body weight and psychological and physiological parameters in food-insecure and food-secure African American women with obesity. We are examining associations between (1) change in body weight collected over 22 weeks and change in psychological and physiological parameters collected 22 weeks apart and (2) changes in psychological and physiological parameters.Exploratory aim: the study will longitudinally examine cyclic patterns in body weight, food insecurity, and stress in food-insecure and food-secure African American women with obesity. Body weight is collected daily to assess average weekly change. Food insecurity and stress are assessed weekly via questionnaires. We are examining weekly patterns of body weight, food insecurity, and stress to determine how changes in body weight are related to episodes of food insecurity and stress. Finally, we are assessing mediation analysis of the psychological questionnaires.

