### Outcome Measures and Study Procedures

#### Overview

The primary outcome of the RESPONSES study is the change in *body weight*. The secondary outcomes include *psychological parameters* (stress; executive function, decision-making, and motivation; and affect and nonhomeostatic eating measured via psychological questionnaires) and *physiological parameters* (cortisol, DHEA-S, CRP, thyroid hormones [thyroid-stimulating hormone, free tri-iodothyronine, and free thyroxine], blood glucose, glycated hemoglobin, and insulin levels measured via blood and urine samples, as well as an allostatic load total score). Table 1 summarizes the data collection schedule of study procedures.

**Table 1 table1:** Schedule of RESPONSES (Effects of Episodic Food Insecurity on Psychological and Physiological Responses in African American Women With Obesity) study procedures.

Study procedure		Screening visit	Clinic visit 1 (week 0)	Remote visit 2 (week 11)	Clinic visit 3 (week 22)
Informed consent and HIPAA^a^ authorization		✓			
Health questionnaire and medical history		✓			
Medication inventory		✓			

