### Planned Statistical Analysis

All available daily body weights will be used for analyses. For aim 1, body weight and psychological and physiological parameters will be analyzed using a mixed effects model with time, food security status, baseline BMI, and age. Models will be checked for both normality and heterogeneity of variance in potential subgroups (eg, age and BMI category). Least squares means and tests for differences by food security group will be the primary results. The analysis of aim 2 will focus on correlations among the outcomes from aim 1. Both Spearman and Pearson correlation coefficients will be used to determine the pairwise relationships among outcomes. Depending on the collinearity among outcomes, factor analysis will also be used to explore these relationships. Analysis of the exploratory aim will determine whether the weekly patterns of change in body weight, food security status, and perceived stress are different by food security group and how well these measures are associated with each other over time.

For aim 1, mixed effects models will be used to model psychological and physiological parameters. Furthermore, a linear mixed effects model will be used to model the daily weight over time. In addition to overall changes in body weight between the groups adjusted for BMI, age, and other baseline covariates, smaller temporal changes (ie, weekly) will also be a focus. Modeling these smaller changes should account for the increased fluctuations in the weight of the food-insecure women.

For aim 2, mixed effects models will assess how daily weight change is associated with changes in psychological and physiological parameters. Initial weight, overall weight change, and weekly weight change will all be considered as predictors in addition to more exploratory weight variables, such as the number of days significantly above or below starting weight or average absolute daily weight changes. These variables will be interacted with food security status (group) to determine whether the weight changes have greater effect on food-insecure women.

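### Aim 2's pairwise correlations have no stated adjustment for cohort, and the 0.40 power claim implies pooling, so a cohort difference in both variables can appear as an association

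*Protocol article*

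**What the plan says.** The study enrols two cohorts of equal size, "30 (50%) who report being food insecure and 30 (50%) who report being food secure at baseline" (Overview of Study Design). Aim 2 is to "examine associations between changes in body weight and psychological and physiological parameters in food-insecure and food-secure African American women with obesity" (Aims). It has two parts: weight change against change in the parameters, and changes in the psychological and physiological parameters among themselves.

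For this aim the power section gives one sentence: "this study is also powered to detect a correlation as small as 0.40 for aim 2" (Sample Size and Statistical Power). No alpha, power level or analysis set is attached to it. The 80% target in that section is stated for body weight.

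Planned Statistical Analysis describes two kinds of aim 2 analysis:

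- Correlations among the aim 1 outcomes: "Both Spearman and Pearson correlation coefficients will be used to determine the pairwise relationships among outcomes". Factor analysis may follow, depending on collinearity. Cohort is not mentioned.
- Mixed models with several weight variables as predictors: "These variables will be interacted with food security status (group) to determine whether the weight changes have greater effect on food-insecure women". Here cohort is in the model.

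Under Aims, the aim 1 hypothesis is that food-insecure women will gain weight and show parameter changes in the direction of more stress, relative to food-secure women.

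**The concern.** A correlation computed over two cohorts mixes two things: the association among women within a cohort, and the difference between the cohort means. Aim 2 is about the first. If aim 1's hypothesis is true, the second is not zero for the pairs that matter most, such as weight change with change in stress. The raw coefficient would then count the aim 1 result again as an association between outcomes.

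The size of the between-cohort part also depends on the mix of cohorts. It is proportional to p(1 − p), where p is the fraction in one cohort, and so is largest at the 1:1 enrolment used here.

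At stake is the interpretation. The study sets out to identify mechanisms linking food insecurity and obesity, and a correlation produced by group means alone is not evidence of one. Separately, a reader may take the power sentence to cover all of aim 2, including the group interactions, which it does not.

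**Working it through.** **Inputs.** N = 60 and 30 per cohort (Overview of Study Design); r = 0.40 (Sample Size and Statistical Power); expected weight changes 0.80 and 0.54 kg and SD 0.30 kg (same section), so d = (0.80 − 0.54)/0.30 = 0.87. Assumed, because not stated: two-sided alpha 0.05, 80% as the power target for correlations, all 60 women analysed, approximate bivariate normality.

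**1. The plan's own figure.** By Fisher's z, power = Φ(atanh(r)·√(n − 3) − 1.96).

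- n = 60: 0.4236 × √57 = 3.20; Φ(1.24) = 89% (simulation 90%; Spearman about 87%).
- N needed for 80%: ((1.96 + 0.842)/0.4236)² + 3 = 46.7, so 47 women.
- Smallest r with 80% power at N = 60: tanh(2.802/√57) = 0.355.

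The figure is correct for one test on all 60 women, with room for about 13 losses.

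**2. It cannot refer to a single cohort.**

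- n = 30: 0.4236 × √27 = 2.20; Φ(0.24) = 60% (simulation 61%).
- Smallest r with 80% power at n = 30: tanh(2.802/√27) = 0.49.

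**3. Group interactions.** As a simple stand-in, compare two independent correlations, 0.40 in one cohort and 0 in the other. The standard error of the difference in z is √(2/27) = 0.272. Then 0.4236/0.272 = 1.56, and Φ(1.56 − 1.96) = 34%.

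**4. Correlation induced by pooling.** Take two cohorts in ratio 1:1, no within-cohort correlation, and mean differences d₁ and d₂ in within-cohort SD units. The pooled correlation is

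r = (d₁d₂/4) / √[(1 + d₁²/4)(1 + d₂²/4)].

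| d₁ (weight) | d₂ (second variable, assumed) | induced r | rejected at 5%, N = 60 | by simulation |
|---|---|---|---|---|
| 0.87 | 0.87 | 0.16 | 23% | 23% |
| 0.87 | 0.5 | 0.10 | 11% | 11% |
| 0.5 | 0.5 | 0.06 | 7% | 7% |
| 0.87 | 0 | 0 | 5% | 5% |

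First row in full: 0.8667²/4 = 0.188 and 0.188/1.188 = 0.158; atanh(0.158) × √57 = 1.20; Φ(1.20 − 1.96), plus a negligible opposite tail, is about 23%.

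**5. Cost of adjusting.** Each covariate removes one degree of freedom. Group only: 0.4236 × √56 = 3.17; Φ(1.21) = 89%. Group, age and baseline BMI: 0.4236 × √54 = 3.11; Φ(1.15) = 88%.

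**The case against.** The strongest reply is that the article never says the correlations ignore cohort. It names both cohorts in aim 2, and the full protocol or analysis plan may adjust. That is fair, and the point is conditional on it. But the 0.40 claim does not reach 80% power within a cohort, and the same section brings group into the mixed models while leaving it out of the correlations. Pooling without adjustment is therefore the natural reading.

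A second reply is that the mixed models already handle group for weight against the parameters. That stands for those models. It does not change the raw correlations reported beside them. Nor does it reach the second part of aim 2, the parameters among themselves, for which no mixed model is described.

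A third is that the second effect size is not in the documents. This also stands. Weight is the only outcome with a stated difference, and at 0.5 SD for both variables the effect is small.

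Three stronger readings are tempting, and the documents do not support them:

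- That the 0.40 figure is wrong. It reproduces with a margin; it claims power for one correlation and promises nothing for subgroups, interactions or a family of tests.
- That pooling by itself creates spurious correlation, or that the results will be full of group artefacts. Both variables must differ in mean change; if either does not, the test keeps its 5% level. Even the largest case shown gives r = 0.16, far below 0.40.
- That the many outcome pairs, with two coefficients each and no stated multiplicity rule, are a fault. Error control for secondary correlations, the choice of a deciding coefficient and a short list of key pairs are commonly left to an analysis plan, which is not shown here. They form no part of this point.

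**Conclusion.** The point holds in a limited form. As written, the aim 2 correlations are most naturally read as pooled and unadjusted. Under the study's own hypothesis they can then be non-zero with no association inside either cohort. The excess is conditional: 23% rejection instead of 5% if both variables differ by 0.87 SD, 7% if both differ by 0.5 SD, and none if either does not differ. The 0.87 comes from the plan for weight only; its use for a second variable is an assumption, as are the 5% two-sided level, normality and complete data.

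The power sentence is correct but unlabelled. It applies to one test on all 60 women. It does not extend to correlations within a cohort or to the planned interactions, so a null interaction should not be read as evidence that the cohorts are alike. The 34% for interactions is specific to the contrast of 0.40 with 0 and stands in for the mixed-model term. This is a secondary aim, but the improvement is specific and nearly free.

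**What to change.** 1. In Planned Statistical Analysis, state that the aim 2 correlations are partial correlations adjusted for food security group, with age and baseline BMI as in the aim 1 model. For Spearman, apply the same adjustment to the ranks. If raw pooled coefficients are also shown, label them as containing the between-cohort difference.
2. In Sample Size and Statistical Power, label the 0.40 figure as a single two-sided 5% test on all 60 women (89% power; smallest r with 80% power about 0.36). Add that it does not cover within-cohort correlations or the interactions with group, and give the lower power for these.

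The cost is two or three sentences and a small change to the analysis code. No new data are needed: group, age and BMI are recorded at baseline for all 60 women. Power for r = 0.40 falls by about one to two percentage points.
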